### Sample size and power

The sample size of 19 RACFs was deemed to have sufficient statistical power. To estimate the statistical power of the helix, counterbalanced, three-strategy, and three-context area (medication type) trial design, we performed 1000 Monte Carlo simulations using Stata/SE Statistical Software: Release 17.0 (StataCorp. 2021). The sample size analysis was conducted at the RACF level based on the primary outcome (i.e. proportion of RACF-level Guideline concordant use of antipsychotics, benzodiazepines and antidepressants). The sample size was based on conducting analysis using a linear mixed model employing fixed, categorical factors for medication type and guideline implementation strategy and RACF as a random intercept. We assumed a minimum important effect size of an absolute change in the proportion of concordant medication category takers of 5% for the level 2 strategy relative to level 1 strategy and of 15% for the level 3 strategy relative to level 1 strategy. Given these assumptions, our sample size of 19 RACFs provides > 99% power to detect the absolute change in proportion of concordant medication category takers of 15% and 81% power to detect the absolute change in proportion of 5%.

### Analysis plan

#### Effectiveness analysis

All primary analyses will be conducted using the intention-to-treat (ITT) principle. Level 3 intervention will be compared to level 1 and level 2 at the 6-month time point as a primary outcome (Table 4).

Per protocol analysis will also be undertaken with the per protocol set including all RACFs without a major protocol deviation. Major protocol deviations may include, but are not limited to, the following:Loss of knowledge brokerIncomplete delivery of intervention (e.g. local action plans, QUM service)

We anticipate that the primary analysis will be conducted using a linear mixed model treating the RACF as a random effect, with the strategy level and medication contexts as fixed effects. Multiple imputation will be used to impute missing covariate values where necessary. Data will be analysed using Stata/SE Statistical Software: Release 17.0 (StataCorp. 2021).

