## Background

Persistent high rates of psychotropic medication use in residential aged care facilities (RACFs) remain a concern for residents, caregivers and other stakeholders. This is despite a lack of evidence supporting benefits of psychotropic medication but well-documented risks of harm. More than 60% of Australian RACF residents use regular psychotropic medications, with 41% prescribed antidepressants, 22% antipsychotics and 22% benzodiazepines on a regular basis [1]. Psychotropic medication prevalence is also highly variable, with a study across 27 RACFs in the state of Victoria reporting antipsychotic prevalence ranged from 0 to 95% (mean 32%) and antidepressant prevalence ranged from 10 to 89% (mean 48%) [2].

The American Psychiatric Association [3], European Academy of Neurology [4] and Australian Clinical Practice Guidelines and Principles of Care for People with Dementia [5] recommend avoiding antipsychotics in people living with dementia. Evidence suggests antipsychotics are associated with increased risk of cardiovascular and cerebrovascular events, falls and death [6, 7]. Benzodiazepines are associated with minimal and short-term improvements in sleep disturbances but also with an increased risk of hip fracture [8] and falls [9]. Antidepressants have uncertain benefits in people living with dementia and have been associated with adverse events including dry mouth, dizziness and falls [10].

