### Data collection

Data collection from the RACFs will occur at baseline and quarterly (3, 6, 9 and 12 months; Table 4). The data collected in this trial will include de-identified data extracted from existing routinely collected data sources within each RACF. Existing data sources will include National Aged Care Mandatory Quality Indicator Program records [33], psychotropic registers [34], prescribing and medication administration records, nursing progress notes, medical records and behaviour support plans. Data will be collected by trained aged care nurses, health or care professionals, employed or contracted by each of the participating aged care provider organisations, who will be blinded to the RACF group allocations. One or more nurses, health or care professionals per participating aged care provider organisation will attend an online training webinar on data collection led by the Project Management Team. Data will be collected and stored on a secure server by Monash University using REDCap™ (Research Electronic Data Capture), a secure web-based software platform designed to support data capture for research studies [35, 36]. Trial data will be stored for a minimum of 15 years after publication of result in accordance with Australian NHMRC and Monash University guidance for medical research involving clinical trials. The final trial dataset will only be accessible to the trial investigators and statistician or epidemiologist.

**Table 4 Tab4:** SPIRIT diagram — schedule of enrolment, intervention, and assessment for the EMBRACE trial

Trial period								Data source
**Time point**	Enrolment	Allocation	Intervention period					
	*-t*	*-t*	0	3	6	9	12	

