The EMBRACE trial uses a helix-counterbalanced study design, which provides several advantages over cluster randomised or stepped-wedge designs [19]. Firstly, it is not necessary to adjust for RACF characteristics because each RACF provides data for each implementation strategy. Secondly, all participating RACFs will receive all implementation strategies. This will help to maintain engagement of those RACFs which would otherwise have been randomised to the control group. Finally, the implementation strategies can be delivered simultaneously rather than sequentially as in a stepped-wedge design.

The EMBRACE trial will generate important knowledge about guideline implementation and knowledge brokers that can be used to scale up the intervention across Australia, inform application to other therapeutic areas and contexts, and improve the delivery of healthcare to all residents living in RACFs.

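### The primary model as stated does not use the baseline concordance collected for each RACF and drug class, which costs precision in the strategy contrasts

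*Protocol article*

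**What the plan says.** The Effectiveness analysis section expects the primary analysis to be a "linear mixed model treating the RACF as a random effect, with the strategy level and medication contexts as fixed effects". The Sample size and power section simulated the same structure, a "linear mixed model employing fixed, categorical factors for medication type and guideline implementation strategy and RACF as a random intercept". No baseline term appears in either. The only mention of covariates is that missing covariate values will be multiply imputed; none is named.

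Baseline values will exist. "Data collection from the RACFs will occur at baseline and quarterly", and Table 4 marks RACF-level concordance at time 0 as well as at 3, 6, 9 and 12 months. Tables 5, 6 and 7 give a separate indicator set for each drug class, so each RACF has three baseline values.

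Table 1 assigns each RACF all three strategies, each for a different class. In Group A, for example, level 3 is antipsychotics, level 2 benzodiazepines and level 1 antidepressants. The Discussion, comparing the helix design with cluster and stepped-wedge designs, says that "it is not necessary to adjust for RACF characteristics because each RACF provides data for each implementation strategy".

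**The concern.** The Discussion's argument is that each RACF serves as its own control. That holds for whatever raises or lowers concordance equally in all three classes of an RACF. It does not hold for a pattern across classes, such as an RACF with good antipsychotic consent records and poor benzodiazepine review. Because strategy is tied to class within an RACF, that pattern enters the comparison of level 3 with level 1 or level 2. The RACF effect cannot remove it, and the context effect removes only the average difference between classes.

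With 19 RACFs there are only six or seven per group, so such patterns can differ between groups by chance. Baseline concordance by RACF and class measures them directly and is already to be collected. Leaving it out makes the primary confidence intervals wider than they need to be, to an extent that depends on how stable the patterns are over 6 months.

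**Working it through.** **Inputs from the protocol.** "The sample size of 19 RACFs was deemed to have sufficient statistical power"; with three classes this gives 19 x 3 = 57 cells at 6 months. The effects assumed are "an absolute change in the proportion of concordant medication category takers of 5% for the level 2 strategy relative to level 1 strategy" and "15% for the level 3 strategy relative to level 1 strategy", which imply 15 - 5 = 10 points for level 3 v level 2. Stated power is 81% for 5 points and above 99% for 15 points. The primary comparisons are level 3 v level 1 and level 3 v level 2.

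**Not in the protocol, so assumed.** Two-sided 5% significance level; groups of 7, 6 and 6; rho from 0 to 0.8. No residual SD is given.

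**1. What stays in a contrast.** Write 6-month concordance in RACF i and class j as

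y_ij = m + u_i + c_j + s_k + d_ij + e_ij,

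with u_i the RACF effect, c_j the class average, s_k the strategy effect, d_ij the RACF-by-class departure and e_ij sampling error. In a Group A RACF, level 3 minus level 1 is

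(c_AP - c_AD) + (s_3 - s_1) + (d_AP - d_AD) + (e_AP - e_AD).

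u_i cancels and the context term takes out c_AP - c_AD. The d difference remains. Baseline concordance in the same cell carries information on d_ij.

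**2. The plan's own power.** A within-RACF contrast has SE = SD x sqrt(2/19) = 0.3244 x SD. The exact 7/6/6 design matrix gives 0.3249 x SD. Residual df = 57 - (19 + 2 + 2) = 34.
- 81% power at 5 points requires SE = 5/(1.960 + 0.878) = 1.76 points.
- The implied residual SD is 1.76/0.3244 = 5.43 points (normal), or 5.27 using the t distribution on 34 df.
- With that SD, power for 15 and for 10 points exceeds 99.9%.

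The two stated powers therefore agree with each other. They cannot be reproduced forward, because the SD behind them is not given.

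**3. Adding the cell's baseline.** The SE is multiplied by about sqrt(1 - rho^2), and one of the 34 df is used. Simulation of the 57 cells (SD 5.27, 4000 runs per setting, RACF taken as fixed so that the baseline slope is the within-RACF one) gave:

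| rho | sqrt(1 - rho^2) | 95% CI width, level 3 v 1: unadjusted | adjusted | change | power for 5 points (level 2 v 1): unadjusted | adjusted |
|---|---|---|---|---|---|---|
| 0 | 1.000 | 6.90 | 7.01 | +1.6% | 0.803 | 0.792 |
| 0.3 | 0.954 | 6.89 | 6.67 | -3.2% | 0.810 | 0.841 |
| 0.5 | 0.866 | 6.91 | 6.07 | -12.2% | 0.809 | 0.894 |
| 0.7 | 0.714 | 6.91 | 5.02 | -27.4% | 0.798 | 0.975 |
| 0.8 | 0.600 | 6.91 | 4.21 | -39.1% | 0.809 | 0.998 |

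The gain falls slightly short of the formula because the slope has to be estimated. Power for both primary contrasts is above 0.999 with or without adjustment.

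**4. If the residual SD is larger.** Binomial sampling alone gives sqrt(0.2 x 0.8/20) = 8.9 points in a cell with 20 users and 20% concordance (assumed figures), already above 5.3. With an assumed residual SD of 12 points (3000 runs), power for level 3 v level 2 (10 points) goes from 0.69 to 0.80 at rho 0.5, and from 0.71 to 0.94 at rho 0.7. The proportional narrowing of the interval is the same as in the table.

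**5. Which rho is reachable.** Rho refers to observed proportions, so sampling noise lowers it. Take 18 users at 30% concordance (assumed): the binomial variance is 0.3 x 0.7/18 = 0.0117, or 117 in squared points. With a fully stable RACF-by-class SD of 5, 10 or 15 points and independent sampling, rho is 25/142 = 0.18, 100/217 = 0.46 or 225/342 = 0.66. Patterns that drift lower it; residents measured at both times raise it.

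**The case against.** The strongest reply is that this is a condensed article. The model is introduced as what the investigators expect to use, covariates are foreseen in the imputation sentence, and an analysis plan not shown here may list baseline concordance. That is fair as far as it goes: the protocol does not exclude a baseline term. But it does name the random and fixed effects, and it powers the trial on the same model. The point is that this named model can be improved with data already planned, not that detail is absent.

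Second, a reader might take the Discussion sentence as a decision against baseline adjustment. The text does not support that. The sentence concerns RACF characteristics, is correct for those acting equally on all classes, and says nothing about the baseline outcome. Its only fault is that it is worded too broadly.

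Third, on the protocol's own figures both primary contrasts have ample power either way. That stands as long as the residual SD really is near 5.3 points. Level 2 v level 1, where the table shows a gain in power, is not a named primary comparison.

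Fourth, the Background reports wide ranges of antipsychotic and antidepressant use across 27 RACFs, and a reader might infer large RACF-by-class differences from them. Those figures describe prevalence of use, not concordance, and show spread between RACFs within a class. They do not show what remains once a common RACF effect is removed, so they are not used here.

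**Conclusion.** The point holds as one of efficiency. The stated model leaves RACF-by-class baseline differences in the residual of every strategy contrast, and a covariate that would remove part of them is already being collected. At an assumed rho of 0.3, 0.5 or 0.7 the confidence interval would be about 3%, 12% or 27% narrower; at rho 0 it would be under 2% wider. The protocol supports no particular rho, so the true gain may be anywhere from nothing to substantial.

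It would be too strong to call the stated analysis biased. Allocation is randomised within matched blocks and counterbalanced, so the contrasts are unbiased without a baseline term. A chance imbalance affects a given estimate only in proportion to the slope of 6-month on baseline concordance, and its random variation is already in the standard error. Nor do the documents show that the primary comparisons lack power: the SD-12 results in the working rest on an assumption well above the implied SD. The case for the change is that the possible gain is useful and the possible loss very small.

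**What to change.** In the Effectiveness analysis section, add to the primary model one fixed covariate: baseline concordance of the same RACF and drug class. State this before outcome data are seen, so that it is not a later choice.

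Say also that the baseline value reflects the period before any strategy is delivered. Table 3 puts the first QUM session and the start of knowledge broker services at baseline, and Table 4 marks both intervention and concordance assessment at time 0, so the order has to be explicit.

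In the Discussion, limit the remark on adjustment to RACF characteristics that act equally on all three drug classes.

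The cost is two or three sentences, no new data and one of about 34 degrees of freedom. An RACF with no users of a class at baseline would have no value for that cell; the imputation already foreseen for covariates can cover it if the plan says so.

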#### RACF Guideline concordance

Trained nurses and health or care professionals will assess Guideline concordance using a standard data collection form completed online (preferred) or in a paper-based version. The data collection form will include questions to assess concordance with indicators for each medication context (Tables 5, 6 and 7). This will require trained nurses and health or care professionals at each participating aged care provider organisation to assign each resident a unique trial identification number. Each aged care provider organisation will securely store the spreadsheet of each resident’s trial identification number, and this will only be accessed by appropriate staff employed by the aged care provider organisation, as needed for care delivery. The Project Management Team will not have access to this information and will not be able to identify residents.

**Table 5 Tab5:** Indicators to assess aggregate RACF-level concordance: antipsychotics

	***Indicators to assess aggregate RACF-level concordance***	***Corresponding Guideline recommendations***
1	Residents using antipsychotics have documentation of experiencing distressing psychotic symptoms and/or aggression/agitation within the past 12 weeks that represents a direct threat to either the resident or other residents, staff, or family for the resident’s prescription of the antipsychotic	GPS 9; CR 3
2	Residents using antipsychotics have documentation of individually targeted non-pharmacological management strategies to manage distressing psychotic symptoms and/or aggression/agitation that are currently in place	GPS 6
3	Residents using antipsychotics are using a second-generation antipsychotic	CR 1
4	Residents using antipsychotics have documentation of informed consent for use of the antipsychotic	GPS 8
5	Residents using antipsychotics have a documented date of next review for antipsychotic treatment effectiveness	GPS 10
6	Residents using antipsychotics have a current antipsychotic adverse event monitoring protocol in place	GPS 20
7	Residents using antipsychotics have used the current antipsychotic for less than 12 weeks	GPS 19; GPS 21
8	Residents using antipsychotics for more than 12 weeks are currently having the antipsychotic dose tapered	GPS 19; GPS 23

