9	Residents using antipsychotics for more than 12 weeks and not currently tapering have documentation that the resident has been reviewed by either a psychiatrist or geriatrician, a formal documented discussion between the prescriber and a psychiatrist or geriatrician in which both practitioners agree or a documented clinical review involving the prescriber and at least one other medical practitioner in which both practitioners agree	GPS 19; GPS 21; GPS 22

Abbreviations: *RACF*, residential aged care facility; *GPS*, good practice statement; *CR*, conditional recommendation. GPS and CR refer to those in the Clinical Practice Guidelines for the Appropriate Use of Psychotropic Medications in People Living with Dementia and in Residential Aged Care

**Table 6 Tab6:** Indicators to assess aggregate RACF-level concordance: benzodiazepines for sleep disturbance

	***Indicators to assess aggregate RACF-level concordance***	***Corresponding Guideline recommendations***
1	Residents using benzodiazepines have documentation of individually targeted non-pharmacological management strategies for sleep disturbance that were trialled for an adequate period of time prior to commencing the benzodiazepine	GPS 26
2	Residents using benzodiazepines have documentation of individually targeted non-pharmacological management strategies to manage sleep disturbance that are currently in place	GPS 6
3	Residents using benzodiazepines have documentation of informed consent for use of the benzodiazepine	GPS 8
4	Residents using benzodiazepines have a documented date of next review for benzodiazepine treatment effectiveness	GPS 10
5	Residents using benzodiazepines have a current benzodiazepine adverse event monitoring protocol in place	GPS 28
6	Residents using benzodiazepines have used the current benzodiazepine for less than 2 weeks	GPS 26
7	Residents using benzodiazepines for more than 2 weeks are currently having the benzodiazepine dose tapered	GPS 29
8	Residents using benzodiazepines for more than 2 weeks and not currently tapering have documentation of a review of the harms and benefits of benzodiazepine continuation	CR 6

*Abbreviations*: *RACF*, residential aged care facility; *GPS*, good practice statement; *CR*, conditional recommendation. GPS and CR refer to those in the Clinical Practice Guidelines for the Appropriate Use of Psychotropic Medications in People Living with Dementia and in Residential Aged Care

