**Table 7 Tab7:** Indicators to assess aggregate RACF-level concordance: antidepressants

	***Indicators to assess aggregate RACF-level concordance***	***Corresponding Guideline recommendations***
1	Residents using antidepressants have documentation of moderate or severe major depressive disorder	CR 9
2	Residents using antidepressants have documentation of individually targeted non-pharmacological management strategies that are currently in place	GPS 6
3	Residents using antidepressants have documentation of informed consent for use of the antidepressant	GPS 8
4	Residents using antidepressants have a documented date of next review for antidepressant treatment effectiveness	GPS 10
5	Residents using antidepressants have a current antidepressant adverse event monitoring protocol in place	GPS 36
6	Residents using antidepressants have used the current antidepressant for less than 6 months	CR 11
7	Residents using antidepressants for more than 6 months are currently having the antidepressant dose tapered	GPS 37
8	Residents using antidepressants for more than 6 months and not currently tapering have documentation of a review of the harms and benefits of antidepressants continuation	CR 11

*Abbreviations*: *RACF*, residential aged care facility; *GPS*, good practice statement; *CR*, conditional recommendation. GPS and CR refer to those in the Clinical Practice Guidelines for the Appropriate Use of Psychotropic Medications in People Living with Dementia and in Residential Aged Care

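### The primary model fits one strategy effect for all three drug classes; if the effect differs by class, part of that difference enters the residual and makes the strategy intervals conservative

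*Protocol article*

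**What the plan says.** Under Effectiveness analysis, the model is introduced with "We anticipate that the primary analysis will be conducted using a linear mixed model", RACF is a random effect, and the rest of the specification is "with the strategy level and medication contexts as fixed effects". The primary comparisons at 6 months are level 3 with level 1 and level 3 with level 2.

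Under Sample size and power, the simulations use a "linear mixed model employing fixed, categorical factors for medication type and guideline implementation strategy and RACF as a random intercept". One effect is assumed per strategy, whatever the class: 5 points for level 2 v 1 and 15 points for level 3 v 1. With 19 RACFs the stated power is 81% and above 99% respectively.

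The outcome is a composite built separately for each class (Tables 5 to 7). The antipsychotic list has nine indicators and the other two have eight. The duration indicators run on different clocks: "Residents using antipsychotics have used the current antipsychotic for less than 12 weeks", "Residents using benzodiazepines have used the current benzodiazepine for less than 2 weeks" and "Residents using antidepressants have used the current antidepressant for less than 6 months".

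**The concern.** With strategy and context as main effects only, the level 3 v level 1 difference is the same number of percentage points for antipsychotics, benzodiazepines and antidepressants. The three composites differ in content and time limits, so there is no strong reason to expect equal gains on the absolute scale.

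In the counterbalanced square of Table 1, the strategy contrasts are made within RACFs and their standard error comes from the within-RACF residual. A difference in strategy effect between classes that the model does not fit is partly counted as residual noise. The result is wider intervals than the data justify and less power than stated for the smaller effect. The primary estimate is also an average over classes that the plan does not describe as one.

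**Working it through.** **Inputs.** From the article: 19 RACFs, three classes each (57 proportions); the layout of Table 1; planned effects of 5 and 15 points; stated power of 81% and above 99%. Assumed, because the article does not give them: two-sided 5% test, complete data, a 7/6/6 split over groups A/B/C, level 2 effect one third of level 3 in each class, and the class-specific patterns below (order: antipsychotics, benzodiazepines, antidepressants). The between-RACF SD cancels from within-RACF contrasts.

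**1. The plan's own figure.** It cannot be reproduced directly, since no SD is given, so I solved for the SD that it implies. SE = σ√(2/19), with 57 − 19 − 2 − 2 = 34 df.
- Normal approximation: SE = 5/(1.960 + 0.878) = 1.762, so σ = 5.43.
- Noncentral t: σ = 5.28, SE = 1.71, half-width = 2.032 × 1.712 = 3.48 points.

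The same σ gives power above 99.9% for 15 points, so the two stated powers agree with each other.

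**2. Where a class difference goes.** Take level 3 = 25/5/15 and level 2 = 8.33/1.67/5. Removing strategy and class means leaves these interaction terms:

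| Strategy | Antipsychotics | Benzodiazepines | Antidepressants |
|---|---|---|---|
| Level 1 | −4.44 | 4.44 | 0 |
| Level 2 | −1.11 | 1.11 | 0 |
| Level 3 | 5.56 | −5.56 | 0 |

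Total sum of squares = 2(4.44² + 1.11² + 5.56²) = 103.7. Summing the cells that each group receives under Table 1:
- A: 5.56 + 1.11 + 0 = 6.67
- B: −4.44 − 5.56 + 0 = −10
- C: −1.11 + 4.44 + 0 = 3.33

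Between-group part = (6.67² + 10² + 3.33²)/3 = 51.85, which the RACF effect absorbs. The remaining 103.7 − 51.85 = 51.85 stays within RACFs.

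**3. Effect on the standard error.** Expected residual variance = σ² + (19/3 × 51.85)/34 = 27.8 + 9.7. The exact 7/6/6 layout gives 9.61 for the second term. Inflation of the SE = √(1 + 9.61/27.8) = 1.16. The extra term scales with the square of the spread:
- 20/10/15: extra 2.40, inflation 1.04
- 30/0/15: extra 21.6, inflation 1.33
- 25/5/15 with σ = 8: √(1 + 9.61/64) = 1.07

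**4. Simulation check** (20,000 trials per pattern, σ = 5.28). Half-width and coverage are for level 3 v 1; power is for the 5-point level 2 v 1 contrast.

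| Level 3 effects | Half-width, stated model | Half-width, with interaction | Coverage, stated model | Power, stated model | Power, with interaction |
|---|---|---|---|---|---|
| 15/15/15 | 3.46 | 3.47 | 95% | 81% | 81% |
| 20/10/15 | 3.60 | 3.47 | 96% | 79% | 81% |
| 25/5/15 | 4.01 | 3.47 | 97% | 72% | 81% |
| 30/0/15 | 4.61 | 3.46 | 99% | 60% | 81% |

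Other runs of the 25/5/15 pattern give 73%, so read it as 72 to 73%. Power for level 3 v 1 is 100% and for level 3 v 2 at least 99.9% in every row. Under the uneven split the stated model's level 3 v 1 estimate drifts a little from the class average of 15 (expected value 15.28 for 25/5/15 and 15.42 for 30/0/15). The equal-weight contrast does not.

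**5. A harmless pattern.** With level 1 at 0/−5/5, level 2 at 0/10/5 and level 3 at 20/15/10, the whole interaction sum of squares (150 of 150) lies between groups. The half-width is then 3.47 and power 81%, as with no interaction.

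**The case against.** The strongest reply is that nothing here is invalid. Strategy, context and unit as main effects is a conventional analysis of a counterbalanced square; the two sections of the article agree; estimates stay close to the class average; and coverage errs on the safe side. That stands: this is a loss of efficiency, not a bias or a false-positive problem.

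A reader might infer that any difference between classes ends up in the error term. It does not. Differences in the level of concordance go to the context effect, and 2 of the 4 interaction df go to the RACF effect.

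A reader might also infer that the primary comparisons lose their power. The documents do not support that either. The 81% is attached to level 2 v 1, which Effectiveness analysis does not list as primary, and the level 3 contrasts stay above 99% at the planned effects and back-solved SD.

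The size is uncertain. The SD is inferred, a larger SD shrinks the relative widening, and if the SD used in the simulations already contained class-to-class variation then part of the loss is already counted. The effect patterns are assumptions. Tables 5 to 7 also share parallel indicators (current non-pharmacological strategies, consent, review date, adverse-event monitoring), which argues for some similarity of effect.

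Finally, the model is worded as anticipated, and class-specific analyses may sit in an analysis plan that is not shown. Their absence from the article is therefore not counted here. What remains is the form of the model, which the article does state, twice.

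**Conclusion.** The point holds as an inexpensive improvement to a stated method. If strategy effects differ by class, the stated model gives conservative intervals for all strategy contrasts, including both primary ones. Under a 7/6/6 split and a residual SD of about 5.3 points, the half-width grows by about 4% (20/10/15), 16% (25/5/15) or one third (30/0/15). It grows by about 7% for 25/5/15 at an SD of 8, and not at all for a pattern aligned with the groups. The power at risk is the 81% for level 2 v 1. How unequal the class effects will be cannot be known from the documents. The case for change rests on the asymmetry between a possible loss of this size and a cost close to nil.

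**What to change.** Add the strategy-by-context term to the primary model, which amounts to nine group-by-class cell means plus the RACF random effect. Define each strategy contrast (level 3 v 1, level 3 v 2, and level 2 v 1 if reported) as the equal-weight average over the three classes. That average is still a purely within-RACF comparison. Report class-specific effects as secondary, noting that within one class the strategies are compared between different RACFs, so these estimates use between-RACF information and are less precise.

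Cost: one sentence in the analysis plan and 2 of 34 within-RACF df. If the classes do not differ, the interval widens by (2.0369/2.0322) × √(0.10582/0.10556) = 1.0036, about 0.4%. The first ratio is the t quantile at 32 v 34 df. The second is the variance factor of the equal-weight contrast against that of the main-effects contrast under 7/6/6.
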